**Figure 2 Fig2:**
[figure not shown]
**Quadrants of the ostomy site.**

**Table 3 Tab3:** **Classification to score the extent of adhesions covering the stoma**

Score	Observation
0	No adhesions
1	Adhesions present on up to one quadrant of the stoma circle
2	Adhesions present on two quadrants of the stoma circle
3	Adhesions present on three quadrants of the stoma circle
4	Adhesions present on all four quadrants of the stoma circle

One year after randomization, patients in the treatment and control arm will be approached to fill in the same questionnaires on quality of life (SF-36 and DASI) and gastrointestinal complaints (GIC) as preoperatively.

### Ethics and informed consent

This study is conducted in concordance with the principles of the Declaration of Helsinki [17] and Good Clinical Practice guidelines. The protocol was ethically approved by the official Independent Review Board Nijmegen (2013/470) and registered nationally (NL45940.091.13) [15]. A Data and Safety Monitoring Board (DSMB) is established to perform safety surveillance and to perform interim analysis on the safety data, as described.

Patients will be screened in the outpatient clinic for participation in this study by a surgeon in one of the hospitals that will contribute to this study. Each patient must meet the inclusion/exclusion criteria of this trial. All potentially eligible patients are required to sign an informed consent after careful consideration. Patients have to sign the informed consent prior to the index procedure.

### Analysis and sample size

It is hypothesized that the use of the C-Qur™ Film underneath the primary incision reduces the incidence of adhesion at the incision by 30%. This hypothesis is based on the supporting documentation for Seprafilm™ (treatment) versus Control (no treatment) with an adhesion rate of 94% in the control group and 64% in the treatment group [18–22]. We estimate a total drop out of 25% in this study, comprising 10% regular drop out and 15% drop out because of anastomotic leakage. A 15% drop out because of anastomotic leakages is chosen because it is the upper limit of the incidence of this complication. Assuming that the C-Qur™ Film group performs similarly to Seprafilm™, a total of 84 patients, (32 + 10 per group (25% drop out)) would be needed in a randomized study, with 80% power and two-sided alpha = 0.05 in order to detect a 30% reduction in incidence of adhesions.

### Statistics

In general, for continuous variables, the mean, standard deviation, median, IQR, minimum and maximum values will be presented. Groups will be compared using the *t*-test or Mann-Whitney *U* test, as appropriate, based on the distribution of the data. For categorical variables, the frequencies and percentage within each category will be calculated. Groups will be compared using the chi-square or Fisher’s Exact test, as appropriate, based on the expected counts. All available data will be summarized. Demographics, preoperative, perioperative, and postoperative parameters will be reported and compared for both groups. Descriptive statistics will be presented to describe the trial results. Missing data will be evaluated by the investigators, and appropriate action will be undertaken*.* In case of skewed baseline data between groups, results will be corrected for this data.

Our primary analysis will focus on the effectiveness and safety of the C-Qur film between the treatment group and the control group. A chi-square or Fisher’s Exact test will be performed to assess a significant improvement in the incidence, on the Zühlke score of adhesions underneath the incision site, underneath the loop ileostomy or loop/split colostomy site, and for the extent of adhesions underneath the loop ileostomy or loop/split colostomy site as well. The extent of adhesions underneath the incision site and the time needed for takedown of the ileostomy or loop/split colostomy will be compared using a *t*-test. To assess the safety of the C-Qur film the total incidence of postoperative complications will be compared using a *t*-test or a Mann-Whitney *U* test. The mortality and the incidence for each separate complication will be compared using a chi-square or Fisher’s Exact test.

Subgroup analysis will be performed on laparoscopic versus open colorectal resection, and on ileostomy versus colostomy for the incidence, extent and severity of adhesions as described above. Since data collection of the outcome parameters is not blinded when the same surgeon who performed the index procedure also takes down the ostomy, subgroup analysis will be performed for patients with and without blinded data collection of outcome parameters.

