### Intervention

All patients will undergo a colorectal resection with the creation of a temporary loop ileostomy or loop or split colostomy. During this index operation, adhesions, if any, will be mapped. The incidence, location, extent and severity and any treatment of adhesions will be noted. For quantifying the extent of adhesions to the abdominal wall and between organs, the abdominal wall is divided into nine segments and the abdominal cavity into ten segments (Figure 1). Severity of the adhesions will be classified according to the Zühlke classification (Table 2) [16]. Classification of operative wounds based on degree of microbial contamination, number of serosal injuries and number of inadvertent enterotomies will also be noted in the source notes and CRF (case report form).

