### Randomization and blinding

Intra-operatively, the treating surgeon judges whether the patient is eligible for definite inclusion. Prior to formation of the temporary loop ileostomy, loop or split colostomy, included patients will be randomized. Patients will be randomized in a 1:1 fashion to the C-Qur™ Film arm (treatment arm) or the control arm. The randomization will be stratified by operative technique (open or hand-assisted laparoscopy). The allocation sequence will be computer-generated through the web-based program Alea©. A researcher who does not participate in the data analysis will manage the randomization process. This way, the researcher who will perform the data analysis is blinded from treatment allocation. Concealment of treatment allocation and blinding of the surgeon performing the index procedure is not possible because the patient will either get the intervention or does not get an intervention at all. Randomization will be noted in the operation reports, allocation will not.

The patient and doctor at the surgical ward who will complete the case report form during the post-operative period is blinded from treatment allocation. To achieve blinding during the data collection of outcome parameters, the surgeon who will perform the ostomy takedown procedure, will not be the same surgeon as the one who performed the index procedure. Because of the absence of clinical notes regarding allocation, however, the initial surgeon is allowed to do the ostomy takedown in case of man-power or organizational problems.

During the postoperative period after the ostomy takedown, the physician at the ward, who will collect the data regarding the post-operative parameters, will be blinded from the treatment allocation of the patient. The patient will stay blinded for the received treatment.

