### Data recording and follow-up

All included patients will preoperatively fill in two questionnaires on quality of life (SF-36, short-form 36, and DASI, duke activity status index) and one questionnaire on gastro-intestinal complaints (GIC). Preoperatively, information on the following will be collected: age, sex, weight, height, American Society of Anesthesiologists (ASA) classification, smoking status, Revised Cardiac Risk Index (RCRI), chronic obstructive pulmonary disease (COPD)/asthma, diabetes mellitus, primary clinical diagnosis, medical/surgical history, number of previous laparotomies, type of previous laparotomies, number of previous laparoscopies, type of previous laparoscopies, and medication usage. A physical exam will be performed, which includes vital signs and laboratory collection (to include C-reactive protein (CRP), chemistry, hematology and coagulation) and a pregnancy test if the patient is premenopausal.

Classification of operative wounds based on the degree of microbial contamination, the number of serosal injuries and the number of inadvertent enterotomies will be noted in the source notes and CRF.

The type of abdominal closure (layered or mass fascia closure) and suture material used will be noted in the source notes and CRF.

Patients in both groups will receive the same postoperative treatment. Until patients are discharged, the following parameters will be collected: postoperative complications (superficial incisional surgical site infections, deep incisional surgical site infections, anastomotic leakage, intra-abdominal abscess, peritonitis, unexplained fever, fascia dehiscence, wound dehiscence, postoperative hemorrhage, postoperative ileus (POI), pulmonary embolism, pneumonia, urinary tract infection, sepsis, and death), reoperations, first post-operative day of oral food intake, parenteral feeding, number of days parenteral feeding required, tube feeding, number of days tube feeding required, first post-operative day of passing flatus, first post-operative day of passing stool, usage of medication including pain medication, daily VAS-scores, hospital stay, Intensive Care Unit stay and Recovery Unit stay.

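### Covariate adjustment is triggered by observed baseline imbalance instead of being fixed in advance, which wastes precision and leaves the model to be chosen after the data are seen

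*Protocol article*

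**What the plan says.** All references are to the protocol article.

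- **Statistics, adjustment.** The only provision is "In case of skewed baseline data between groups, results will be corrected for this data". No threshold, covariate list or model follows.
- **Statistics, baseline comparison.** "Demographics, preoperative, perioperative, and postoperative parameters will be reported and compared for both groups". The general rules there compare groups by t-test or Mann-Whitney for continuous variables and by chi-square or Fisher for categorical ones.
- **Statistics, primary outcome.** "A chi-square or Fisher’s Exact test will be performed to assess a significant improvement in the incidence". The test is unadjusted.
- **Data recording and follow-up.** "All included patients will preoperatively fill in two questionnaires on quality of life" (SF-36 and DASI), plus a questionnaire on gastrointestinal complaints. The same instruments are repeated one year after randomisation. No specific test is named for them.
- **Intervention.** "During this index operation, adhesions, if any, will be mapped". Location, extent and severity are recorded, over nine abdominal wall segments and ten cavity segments.
- **Randomization and blinding.** Allocation is stratified by operative technique. In Statistics and Discussion, technique appears only as a subgroup analysis.

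**The concern.** The rule selects covariates on the wrong property. Randomisation makes any baseline difference a chance event, and the size of that difference says nothing about whether the variable predicts the outcome. A weak predictor that happens to differ would be adjusted for. A strong predictor that happens to be balanced would be left out, although adjusting for it would still reduce residual variance.

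Two things are at stake. First, the reported model is not fixed before the data are seen, because what counts as skewed, which variables enter and in what form are all open. Second, the trial collects baselines likely to be prognostic and stratifies by technique, yet the stated rule would bring the baselines into the treatment comparison only by accident. The stratification factor has no planned place in the overall comparison.

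**Working it through.** **1. The plan's own figure.** Analysis and sample size gives 94% v 64%, two-sided alpha 0.05, 80% power and 32 per group before drop-out. Full enumeration of the two-sided Fisher test gives power 79.0% at 31 per group and 80.9% at 32, so 32 reproduces. It is used below as the number per arm. It was derived for the binary adhesion outcome, so using it for questionnaires is an assumption.

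**2. How often chance alone would prompt a correction.** Data recording and follow-up lists 16 preoperative items before laboratory values and questionnaires. Assume independent comparisons, each flagged at 5%:

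- P(at least one flagged) = 1 − 0.95^k
- k = 10: 1 − 0.95^10 = 0.40
- k = 20: 1 − 0.95^20 = 0.64

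Any one named prognostic baseline, by contrast, is flagged in only about 5% of trials.

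**3. What the trigger costs for a continuous outcome.** Assumptions not in the article: normal outcome, one baseline covariate with correlation r to the outcome, trigger at p<0.05 on the baseline t-test. The effect is set for nominal 80% unadjusted power: (1.960 + 0.842) × √(2/32) = 0.70 SD. Results from 40,000 simulated trials per scenario, 32 per arm:

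| r | Power, unadjusted | Power, pre-specified ANCOVA | Power, triggered | Type I error, triggered |
|---|---|---|---|---|
| 0.3 | 79.0% | 81.8% | 79.2% | 4.7% |
| 0.5 | 78.8% | 88.5% | 79.7% | 4.3% |
| 0.7 | 78.5% | 97.0% | 80.4% | 3.7% |

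The unadjusted column falls slightly below 80% because the effect was set by the normal approximation. Type I error of pre-specified ANCOVA was 5.0% to 5.1%.

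**4. Hand check.** ANCOVA multiplies the residual variance by 1 − r², so power ≈ Φ(2.802/√(1 − r²) − 1.960):

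- r = 0.3: Φ(2.937 − 1.960) = 83.6%
- r = 0.5: Φ(3.235 − 1.960) = 89.9%
- r = 0.7: Φ(3.923 − 1.960) = 97.5%

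These agree with the simulation, allowing for the normal approximation.

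**5. How far adjustment can go for the primary outcome.** Expected adhesion-free patients are 0.06 × 32 = 1.9 in control and 0.36 × 32 = 11.5 in treatment, about 13 in all. That supports stratification by technique and little else.

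**The case against.** **The article is condensed, and a fuller plan may define the details.** True of details, but this is a stated rule and not a gap. A later plan could define skewed and adjustment would still hang on observed imbalance. Pre-specified adjustment would have to contradict the sentence.

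**One-year quality of life may be analysed with its baseline elsewhere.** This stands in part. A reader might infer that SF-36 and DASI are definitely compared without their baselines. The article does not say so: it names no test for them, and an unadjusted test follows only from rules introduced as general. Nor are the baselines wholly unused, since they are reported and compared. What is missing from the stated rule is their use in the treatment comparison.

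**The figures rest on assumptions.** This stands. The correlation, effect size and p<0.05 trigger are not in the article, and at r = 0.3 the gain is only 81.8 − 79.2 = 2.6 points. They also concern continuous secondary outcomes. A reader might infer a similar power loss for the primary outcome, but that outcome is binary and no such loss has been shown.

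**No type I error inflation is shown.** This also stands. A reader might infer that data-driven adjustment raises the false-positive rate. With one covariate and a fixed trigger the simulated rule is conservative. Free choice of threshold and covariates is a real hazard, but the article gives no set of choices from which to size it.

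**Technique is already handled by subgroup analysis.** The Discussion offers this as control for technique. Separate subgroup results do not adjust the overall comparison.

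**Conclusion.** The point holds as a defect in a stated rule. Adjustment is tied to observed imbalance, with the trigger, covariates and model left open until the data are seen. For continuous secondary outcomes the rule recovers almost none of the precision available from a prognostic baseline: the shortfall in power is 2.6 points at r = 0.3, 8.8 at r = 0.5 and 16.6 at r = 0.7. These figures are illustrative and depend on 32 per arm, a p<0.05 trigger and an effect giving nominal 80% unadjusted power. The demonstrated harm is lost precision and a model not fixed in advance. The sample size is unaffected. The change should be made, and the article reports that inclusion had not started.

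**What to change.** Delete the trigger sentence and keep the baseline table descriptive. Pre-specify the following, whatever the imbalance:

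- **Primary outcome:** a test stratified by operative technique, for example Cochran-Mantel-Haenszel, in exact form if counts are sparse, with no further covariates.
- **One-year SF-36 and DASI:** ANCOVA on the preoperative score plus technique.
- **Gastrointestinal complaints:** Outcome measures lists these as an incidence, so use a binary analysis adjusted for preoperative complaint status.
- **Adhesion severity and extent:** adjust for technique. Add index-operation adhesions in the corresponding segments only if they were recorded before allocation was known, because randomisation is intra-operative, the index surgeon is unblinded and the article does not state the order. Include a short rule linking map segments to the incision and stoma sites.

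The cost is analysis wording only: no new data are needed and the sample size does not change.

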In this study, both laparoscopic and open colorectal resections will be included. In many countries, laparoscopic colorectal resection for benign and malignant diseases has gained popularity [27]. Thus, performing only an open colonic resection study would lower the generalizibility of the results on adhesion prevention. Laparoscopic technique is accompanied by less tissue trauma. Hence, it is suggested that laparoscopic colorectal surgery results in fewer adhesions. A recently published population-based register study specifically addressed readmission rate for clinically apparent adhesions after colorectal surgery, comparing the open and laparoscopic approach [28]. Of the total of 187,148 patients included, 11,013 (5.9%) had laparoscopic resection. With a median follow-up of 31.8 months, overall adhesion-related readmission rate was 8.1%; 8.2% after an open approach versus 6.3% after a laparoscopic approach (*P* <0.001). An important limitation of this study was the higher percentage of emergency operations in the open group compared to the laparoscopic group. The most common underlying disorder for an emergency laparotomy (that is, peritonitis) has a higher adhesion formation propensity. Despite the relative reduction of 23% in the re-admission rate, it should be concluded that clinically relevant consequences of adhesions are substantial also after laparoscopic surgery. A subgroup analysis for open versus laparoscopic resection will be conducted to control for the difference in surgical technique and concomitant adhesion formation.

For the sake of safe and secure placement of the adhesion barrier, only patients undergoing laparoscopic resection with a specimen extraction incision of at least 6 cm will be included in our study. This minimal incisional length was chosen based on previous experience with the C-Qur™ Film. The availability of different sizes of the film and the tissue adherence only at one site improve the placement in narrow spaces. These characteristics provide potentially better handling when compared to the commonly used HA/CMC barrier film in open colorectal surgery.

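### Randomisation is stratified by operative technique, but the primary test ignores the strata, and the subgroup analysis said to control for technique cannot do so

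*Protocol article*

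**What the plan says.** All references are to the protocol article.

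- *Randomization and blinding*: "Patients will be randomized in a 1:1 fashion", and "The randomization will be stratified by operative technique (open or hand-assisted laparoscopy".
- *Statistics*: for adhesion incidence, a chi-square or Fisher's exact test "will be performed to assess a significant improvement in the incidence". No stratified or adjusted form is given. Subgroup analyses by technique are planned for incidence, extent and severity. The only adjustment clause applies if baseline data turn out skewed between the groups.
- *Analysis and sample size*: the plan assumes "an adhesion rate of 94% in the control group and 64% in the treatment group", "with 80% power and two-sided alpha = 0.05", and arrives at "a total of 84 patients, (32 + 10 per group (25% drop out".
- *Discussion*: laparoscopy is described as causing less tissue trauma and is thought to lead to fewer adhesions. Then: "A subgroup analysis for open versus laparoscopic resection will be conducted to control for the difference in surgical technique". No rate of adhesion to the incision is given for either technique.

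**The concern.** Two features of the plan do not fit together.

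1. A factor considered important enough to stratify the allocation is left out of the test that allocation supports. Stratified allocation balances technique across the arms. A pooled test then counts the between-technique variation as noise. If technique is strongly prognostic, the test becomes conservative and loses power; if it is not, almost nothing is lost.
2. The Discussion recognises that technique may matter, but the tool it chooses does not do the job. Splitting the trial by technique gives two stratum-specific comparisons. It leaves the overall comparison unadjusted, and each part is too small to be read alone. No interaction test is mentioned, so a significant result in one technique and a non-significant one in the other could be taken as a real difference.

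The skewed-baseline clause does not close the gap. Stratification is there to prevent skew in technique, so the clause would normally not be triggered by it.

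**Working it through.** **Inputs from the article.** 94% v 64%; two-sided alpha 0.05; 80% power; 32 evaluable per arm; 25% drop-out; 1:1 allocation; two technique strata.

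**Inputs assumed.** The share of open cases (16 of 32 or 22 of 32 per arm), exact balance within strata, and all stratum-specific rates. The article gives none of these.

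**Step 1: the plan's own figure.** Exact enumeration of the unstratified two-sided Fisher test at 94% v 64% gives 79.0% power with 31 per arm and 80.9% with 32. So 32 per arm is reproduced, and it was sized for an unstratified test. Drop-out: 32 / (1 − 0.25) = 42.7 per arm against the stated 42, a rounding difference that does not affect this point.

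**Step 2: the two tests.** Let *c* and *t* be the numbers with adhesions in control and treatment, *m* = *c* + *t*, and *n* the number per arm.

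- Pooled chi-square: X² = (c − t)² · 2n / [m(2n − m)].
- CMH, with *n_k*, *c_k* and *m_k* the per-arm size, control events and total events in stratum *k*: X² = [Σ(c_k − m_k/2)]² / Σ{n_k² m_k(2n_k − m_k) / [(2n_k)²(2n_k − 1)]}.

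Both are without continuity correction and are compared with 3.84. Each scenario is evaluated by summing over all outcomes of the four binomials.

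**Step 3: power with overall rates held at about 94% v 64%, 32 per arm.**

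| Open (control v film) | Hand-assisted (control v film) | Split per arm | Chi-square | CMH |
|---|---|---|---|---|
| 94 v 64 | 94 v 64 | 16/16 | 88.4% | 88.3% |
| 99 v 74 | 89 v 54 | 16/16 | 88.9% | 89.5% |
| 100 v 79 | 88 v 49 | 16/16 | 89.3% | 90.6% |
| 99 v 70 | 83 v 50.8 | 22/10 | 89.0% | 90.3% |
| 99 v 73 | 82.3 v 43 | 22/10 | 89.3% | 91.2% |

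The difference runs from about −0.1 to +2.0 points. It is small because a 94% control rate leaves little room: with equal strata the control rates can differ by at most 12 points (100% v 88%).

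**Step 4: power if technique is strongly prognostic and the overall rates fall.**

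| Open | Hand-assisted | Split | Overall | Chi-square | Fisher | CMH |
|---|---|---|---|---|---|---|
| 98 v 75 | 60 v 30 | 16/16 | 79 v 52.5 | 63.5% | 52.3% | 72.6% |
| 98 v 72 | 60 v 30 | 22/10 | 86 v 59 | 73.1% | 62.6% | 80.3% |

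Overall rates are weighted means, for example (98 + 60)/2 = 79 and (75 + 30)/2 = 52.5. CMH gains 72.6 − 63.5 = 9.1 and 80.3 − 73.1 = 7.2 points over chi-square.

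**Step 5: type I error, 16 per arm per stratum, no film effect.**

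| Open / hand-assisted rate | Chi-square | Fisher | CMH |
|---|---|---|---|
| 79 / 79 | 5.1% | 2.5% | 4.9% |
| 84 / 74 | 4.9% | 2.4% | 4.9% |
| 94 / 64 | 3.6% | 1.6% | 4.9% |
| 97 / 60 | 2.9% | 1.2% | 5.1% |

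With strata 10 points apart, chi-square and CMH coincide. The pooled chi-square is clearly conservative only when the strata are about 30 points apart or more. The low Fisher sizes are partly discreteness: Fisher is at 2.5% even with identical strata.

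**Step 6: the subgroups.** Fisher power for 94% v 64% is 16% with 10 per arm, 42% with 16 and 63% with 22. If the film works equally in both techniques, the chance that exactly one subgroup is significant is 2 × 0.42 × 0.58 = 49% for a 16/16 split. For a 22/10 split it is 0.63 × 0.84 + 0.37 × 0.16 = 59%.

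**The case against.** The strongest reply is that nothing here makes the planned analysis wrong. With balanced strata the pooled test does not favour the film or inflate type I error, and 32 per arm delivers the stated 80% with Fisher as planned. **This stands.**

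Nor does the article show that technique is strongly prognostic for this endpoint. It says only that fewer adhesions are suggested after laparoscopy. Its one comparison is of adhesion-related readmission (8.2% open v 6.3% laparoscopic), with a caveat about emergency operations. The endpoint is adhesion to the incision itself, and the hand-assisted stratum has an incision of at least 6 cm. **This also stands.** A reader might infer from step 4 that ignoring the strata costs this trial 7 to 9 points of power, or that the primary test is conservative as a matter of course. The documents support neither: those results need hand-assisted rates around 60% v 30%, well away from the planning rates. The drop from 88% to about 63% in chi-square power also comes mostly from the changed overall rates, not from the missing stratification.

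Finally, the *Statistics* section lists the subgroup analysis without claiming that it adjusts anything; only the *Discussion* does. Subgroups by a stratification factor are ordinary, and interaction tests and intervals may be left to an analysis plan. **This stands in part.** The absence of an interaction test is not itself an error, and the article nowhere says it will claim efficacy in one technique only. But the stated purpose of the subgroup analysis is still one that the method cannot serve, and this holds whatever the stratum rates are.

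**Conclusion.** The point holds as a modest, low-cost improvement. The design stratifies by technique, the named primary test does not use the strata, and the analysis said to control for technique produces two underpowered stratum results instead of an adjusted overall effect.

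At the protocol's own rates the gain from a CMH test is about 0 to 2 points of power. Larger gains (7 to 9 points), and a pooled chi-square size of about 3% to 3.6%, arise only if technique is strongly prognostic with hand-assisted rates well below 94% v 64%. All stratum shares and rates behind these figures are assumptions. The planned test remains valid and the sample size is unaffected.

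The case for changing rests on asymmetry: CMH costs about 0.1 point if technique is irrelevant, and keeps the size near 5% and recovers power if technique matters.

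**What to change.** 1. In *Statistics*, make the primary test a Cochran-Mantel-Haenszel test stratified by operative technique, in its exact version if cells are sparse (likely with control rates near 94%). Report a Mantel-Haenszel risk difference with a 95% confidence interval.
2. Present the open and hand-assisted subgroups as exploratory estimates with confidence intervals and one treatment-by-technique interaction test, not as separate significance tests.
3. In the *Discussion*, replace the statement that the subgroup analysis controls for technique. Say that the stratified primary analysis does this, and that the subgroups describe whether the effect differs by technique.

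The cost is a few sentences. Technique is already recorded at randomisation, so no new data and no more patients are needed. The change should be made before any outcome data are compared by arm; the article states that inclusion had not started.

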Patients will return 8 to 16 weeks after index surgery to have their ostomy taken down. Clinical follow-up to obtain update(s) on adverse events (AE’s), adhesion-related events, changes in concomitant medications, the presence/absence of surgical site infection (SSI) and the type of SSI (if applicable) will be done during the admission for ileostomy/colostomy takedown. Weight and vital signs will be noted and the following laboratory investigations will be repeated: CRP, sodium (Na), potassium (K), urea, creatinine, hemoglobin, white blood cell count, platelet count, international normalized ratio (INR) and prothrombin time (PT).

Patients in both groups will undergo the same procedure for ostomy closure. To evaluate the adhesions at the loop ileostomy/colostomy site, the incidence, severity and extent of adhesions around the ostomy have to be evaluated during takedown. The time required for takedown of the ostomy is defined as the time from start of the takedown to the time the bowel is repositioned in the abdomen, and this time will be noted on the CRF. The severity of adhesions will be scored according to the Zühlke classification (see Table 2). To assess the extent of adhesions, the ostomy is divided in four quadrants (Figure 2). The extent of adhesions is scored as the number of quadrants containing adhesions (Table 3). After the ileostomy/colostomy takedown is completed, the surgeon will introduce a laparoscope at the ostomy site and evaluate the incidence, extent and severity of adhesions at the incision site and at other areas potentially injured (and covered) during the initial procedure. The severity will be scored according to the Zühlke classification (see Table 2). The extent of adhesions underneath the incision site will be scored through estimation of the area covered by adhesions as a percentage of the total area underneath the incision. The incidence and severity of adhesions at other areas potentially injured during the initial procedure will be scored according to the Zühlke classification (see Table 2).

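### Ordered 0–4 adhesion scores are assigned a test that ignores their order, and the t-test sentence for incision extent and takedown time departs from the plan's own general rule

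*Protocol article*

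**What the plan says.** All references are to the protocol article.

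- **Scales.** Table 2 grades severity (Zühlke) from 0, none, to 4, where organ damage can hardly be avoided. Table 3 grades stoma extent from 0 to 4 by quadrants involved; score 1, for example, is "Adhesions present on up to one quadrant of the stoma circle". Under Data recording and follow-up, incision extent is recorded by "estimation of the area covered by adhesions as a percentage of the total area underneath the incision".
- **Tests for the scores.** The outcome-specific paragraph of Statistics uses chi-square or Fisher's exact test to look for a significant improvement in incidence, on the Zühlke "score of adhesions underneath the incision site, underneath the loop ileostomy or loop/split colostomy site, and for the extent of adhesions" at the stoma.
- **Test for incision extent and takedown time.** The next sentence says that the "extent of adhesions underneath the incision site and the time needed for takedown of the ileostomy or loop/split colostomy will be compared" with a t-test, and gives no alternative.
- **General rule.** The first paragraph of the same section compares continuous variables by t-test or Mann-Whitney U test, depending on how the data are distributed.
- **Status.** Under Outcome measures, severity, extent and takedown time are secondary. The primary outcome is the presence or absence of adhesions at the incision.

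**The concern.** A chi-square or Fisher test on a five-level score gives the same p-value however the levels are relabelled. It asks whether the two distributions differ in any way and spreads its sensitivity over four degrees of freedom. It does not ask whether film patients score lower. Two things follow. A real shift towards milder or less extensive adhesions may be missed more often than it need be. And a rearrangement of scores with no net improvement can come out significant.

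The t-test sentence raises a different issue. Two instructions in one section cover the same outcomes and disagree. The analyst could follow either after seeing the data.

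**Working it through.** **Inputs from the protocol.** The Analysis and sample size section assumes an "adhesion rate of 94% in the control group and 64% in the treatment group", so zeros at the incision are 6% v 36%. It works "with 80% power and two-sided alpha = 0.05" and asks for "a total of 84 patients, (32 + 10 per group (25% drop out", with 1:1 allocation.

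**Plan's own figure.** Exact enumeration of Fisher's test at 94% v 64% gives power of 79.0% at 31 per arm and 80.9% at 32. The 32 evaluable per arm is reproduced, so 32 is used below. The protocol states no power for severity or extent.

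**Assumptions.** The protocol gives no distribution for scores above 0. Four control shapes (scores 0/1/2/3/4) were tried, all with 6% zeros:
- even: 6/23.5/23.5/23.5/23.5%
- mild: 6/40/30/16/8%
- severe: 6/10/20/34/30%
- middle: 6/20/30/28/16%

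A common odds ratio OR moves the film arm by logit P(film ≤ k) = logit P(control ≤ k) + ln OR. The OR that turns 6% zeros into 36% is (0.36/0.64)/(0.06/0.94) = 8.8.

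**General cost of four degrees of freedom.** A signal with 80% power on 1 df has noncentrality (1.96 + 0.8416)² = 7.85. On 4 df the same noncentrality gives 59.5% power; restoring 80% needs 1.52 times as many patients.

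**Worked case (even shape, OR 2.5).** The film arm becomes 13.8/37.4/22.7/15.2/10.9%. The chi-square noncentrality is 32 × Σ(p − q)²/(p + q) = 4.0, which on 4 df gives 32% power. Simulation gives 31%, and 53% for Mann-Whitney.

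**Simulated power at 32 per arm, two-sided 0.05** (Pearson chi-square v Mann-Whitney, 4,000 runs per cell; rounded ranges over the four shapes and repeat runs):

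| Effect | Chi-square | Mann-Whitney | Difference |
|---|---|---|---|
| OR 2.5 | 27–32% | 48–53% | 20–22 points lost |
| OR 3.5 | 49–57% | 75–79% | 22–27 points lost |
| 94% to 64%, plus OR 2 among those with adhesions | 76–79% | 87–88% | about 10 points lost |
| OR 8.8 throughout | 95–98% | 99–100% | 2–5 points lost |
| 94% to 64% only, remaining severity unchanged | 67–70% | 56–60% | about 10 points gained |

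With no effect, chi-square rejected in 3.9–5.0% of runs and Mann-Whitney in 5.0–5.3%.

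**Rearrangement without improvement.** Take the middle control shape and a constructed film arm of 20/20/10/20/30%. The film score is lower in 0.2×0.94 + 0.2×0.74 + 0.1×0.44 + 0.2×0.16 = 0.412 of random pairs. It is higher in 0.2×0.06 + 0.1×0.26 + 0.2×0.56 + 0.3×0.84 = 0.402. Chi-square rejects in about 56–58% of trials, Mann-Whitney in about 5%.

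**Incision extent.** With 6% v 36% zeros and the same assumed distribution of positive values in both arms, t-test v Mann-Whitney power is:
- right-skewed, beta(0.8, 2.4): 30% v 57%
- uniform: 45% v 55%
- symmetric, beta(3, 3): 65% v 56%
- high coverage, beta(3, 1): 75% v 55%

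If extent among those with adhesions also falls moderately (second beta parameter × 1.6), the figures are 76% v 86%, 85% v 88%, 97% v 97% and 95% v 93%. Rejection under no effect stayed near 5% for both tests.

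**Not computed.** Takedown time was not simulated. Nor was stoma extent as such: it shares the five-level structure, so the odds-ratio rows carry over if its control distribution resembles one of those assumed, but the 94%/64% rates are for the incision. Fisher's test on the full five-level table was not simulated either; it also ignores order.

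**The case against.** **The loss depends on the scenario.** This stands. Odds ratios of 2.5 to 3.5 leave only 14% to 18% of film patients free of adhesions, against the 36% planned. In the two single-mechanism scenarios tied to 94% and 64%, the loss is 2 to 5 points or becomes a gain of about 10. However, the scenario that favours chi-square, in which incidence falls and nothing else changes, is the effect the primary binary comparison already tests. A severity score adds information only if the remaining adhesions become milder, and once that is included the rank test leads again.

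**The Zühlke clause may mean presence only.** It can be read as score 0 v above 0, since the protocol also records incidence with that scale. Chi-square would then be right, but severity would have no outcome-specific test. The stoma-extent clause has no such ambiguity.

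**Direction would still be visible.** Category frequencies are to be reported, so a reader could see which way scores moved. That helps description; it does not make the p-value a test of improvement.

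**Stronger readings that fail.** A reader might infer that these outcomes lose much of their power whatever the effect; the table shows otherwise. A reader might also infer that the t-test is wrong for incision extent because of its zeros. Zeros are 6% in controls and about 21% pooled, the t-test holds its type I error, and it ranges from 27 points worse to 20 points better. Nor does the protocol rank these outcomes as key: it gives an unranked list of secondary measures.

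**Conclusion.** The point holds in a limited form. Stoma extent, and on the natural reading Zühlke severity, are ordered scores given a test that ignores order. At 32 per arm this costs about 20 to 27 points of power for a moderate shift along the scale and about 10 for a mixed effect. It costs little for a very large common odds ratio, and it is a gain if only incidence moves. These sizes rest on assumed score distributions.

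For incision extent and takedown time the finding is an inconsistency between two sentences of one section. No power gain can be claimed for either test: for incision extent the direction turns on a distribution the protocol does not give, and takedown time was not examined.

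Only secondary outcomes are involved. The primary comparison and its sample size are untouched.

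**What to change.** 1. Keep chi-square or Fisher's exact test for incidence, stated explicitly as score 0 v above 0.
2. Compare the Zühlke severity score and the stoma-extent score with an order-respecting method: Mann-Whitney, preferably stratified by operative technique because randomization is, or a proportional-odds model. Report an effect estimate with a 95% confidence interval, such as the common odds ratio or the probability of a lower score.
3. For incision extent and for takedown time, pre-specify one method each and make the outcome-specific sentence agree with the general rule.

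This changes analysis wording only; the article states that inclusion has not started. The price is some power on the scores, about 10 points in the severity scenarios above, if the film abolishes adhesions without making the remaining ones milder. The incidence test covers that case.
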